The systematic detection of physical impairment to be able to intervene in the negative vicious circle towards dependency is an important public health goal. Screening and prevention are 2 of the core tasks of GPs, which are often the first medical contact with older patients. There is, however, no guideline or recommendation to screen the risk of mobility limitation in older adults in primary care [25]. Mobility assessment in clinical general practice should be performed using simple, easy, and quick tools. Several tools have been developed to detect loss of mobility; identifying functional complaints in patients with mobility difficulties has proven to be a valid screening tool for detecting subsequent loss of mobility [11, 26, 27].

The aim of this study is to assess the benefits of a multimodal intervention for older adults with complaints of reduced mobility, screened systematically in primary care. The main objective of this study will be to evaluate between the control and intervention groups change in mobility and muscular force at 6 and 12 months of follow-up, evaluate physical performance, nutritional status, quality of life, and autonomy.

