## Methods

### Study design

PRISME-3P is a national, multicenter, and cluster randomized trial conducted in France (Fig. 1). GPs will be randomly assigned to the intervention group or to the control group. Recruitment and inclusion will be performed by GPs and the intervention will take place at the hospital and home of the patient. The planned inclusion period is 24 months with 12 months follow-up.

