**Fig. 1 Fig1:**
[figure not shown]
Design of the PRISME 3P randomized controlled trial

In both groups, GPs will perform a consultation for inclusion at baseline and two evaluations at 6 and 12 months thereafter. In the intervention group, an initial blood test will be performed (blood cell count, CRP, pre-albuminemia, and albuminemia). Follow-up will include two visits to the allocated study hospital outpatient clinic (within 2 weeks and at 3 months from inclusion) and 3 visits to the GP (at 3, 6, and 12 months from inclusion). All data collected will be notified by the GPS on the case report form (CRF).

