### Outcomes and measurements (Table 3)

#### Primary outcome

The primary outcome will be the difference in SPPB scores between inclusion and 6-month visits. To allow comparison, the SPPB will be evaluated by the same GP as far as possible. The SPPB measure reflects the performance status in 3 dimensions: balance, gait, strength/endurance are evaluated by examining ability to stand with the feet together in the side-by-side, semi-tandem and tandem positions, time to walk 4 or 6 m, and time to rise from a chair and return to the seated position 5 times [39].

**Table 3 Tab3:** Schedule of outcome assessments

	Baseline	Intervention Group			Control Group	
		M 3	M 6	M 12	M 6	M 12
SPPB score	X	X	X	X	X	X
Walk test distance	X		X	X	X	X
SPPB	X	X	X	X	X	X
Physical activity	X		X	X	X	X
ADL/IADL	X		X	X	X	X
SF 12	X		X	X	X	X
Serious falls assessments	X		X	X	X	X
Hospitalization	X			X		X
Institutionalization				X		X
Weight, BMI	X	X	X	X	X	X
MNA	X					
Social score	X					
Charlson Index	X					
Medication inventory	X					

*PASE* Physical Activity Scale for the Elderly, *SF12* 12-Item Short Form Health Survey, *BMI* Body Mass Index, *MNA* Mini Nutritional Assessment, *CRP* C-Reactive Protein, *GDS* Geriatric Depression Scale, *GP* General Practitioners, *EPICES Evaluation de la précarité et des Inégalités de santé dans les centres de santé* (in French)

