#### Secondary outcomes

The change of the secondary outcomes between the inclusion, 6, and 12-month follow-up will be analyzed. Secondary outcomes are: physical performance evaluated by the PASE [30] and sedentary behavior inspired by Gardiner et al. [31], and the distance walking; autonomy evaluated by the ADL and IADL [32]; quality of life evaluated by the SF-12 scale [33]; the number of serious injuries, hospitalizations, and institutionalizations, falls with healthcare consumption; nutritional status: weight, BMI, albuminemia (adjusted on CRP level) and MNA [34].

Additional outcomes will estimate prevalence of patients over 70 years of age with mobility limitation, adherence of patient and GPs to the program, and describe geriatric diagnosis after the consultation for the intervention group.

At baseline, GPs will collect data from the patients social environment EPICES score) comorbidities (Charlson index) [37], depression symptoms (GDS) [38], and medication inventory.

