### Secondary outcomes

The analysis used for the primary outcome will be used to evaluate the change of the secondary outcomes between the inclusion and the 6-month follow-up visit.

The analysis of the change of secondary outcomes in the interventional group will be performed using a longitudinal mixed effect linear model with a fixed period effect and as random effects: the center, the GP, and the patient nested within the GP. This analysis will be adjusted on the age at inclusion.

A univariate analysis will be performed using a longitudinal mixed effect linear model to identify the factors associated with the SPPB result at 6 months in the interventional group. The model will include as random effects the center, the GP and the patient nested within the GP, and as fixed effect the corresponding factor. This analysis will provide the effect estimation of each factor with its 95% confidence intervals. The independent factors found significant in this univariate analysis will be included in a multivariate analysis.

All analysis will be performed using the statistical analysis program SAS® version 9.4 (SAS Institute Inc., Cary, NC, USA), and the R program, version 3.3.1 (R foundation, Vienna, Austria).

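### The objective compares arms at 6 and 12 months, but no committed analysis gives a 12-month between-arm contrast

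*Protocol article*

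**What the plan says.** All references are to the protocol article.

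- **Objective (end of Background).** The main objective is to "evaluate between the control and intervention groups change in mobility and muscular force at 6 and 12 months of follow-up".
- **Study design.** "The planned inclusion period is 24 months with 12 months follow-up". For both groups, "GPs will perform a consultation for inclusion at baseline and two evaluations at 6 and 12 months thereafter".
- **Outcomes and measurements, Primary outcome.** "The primary outcome will be the difference in SPPB scores between inclusion and 6-month visits".
- **Outcomes and measurements, Secondary outcomes.** "The change of the secondary outcomes between the inclusion, 6, and 12-month follow-up will be analyzed". The list includes activity, walking distance, ADL/IADL, SF-12, injuries and falls, hospitalizations, institutionalizations and nutritional status. SPPB at 12 months is not in it.
- **Table 3.** Both arms have month-6 and month-12 columns.
- **Statistical analyses, Primary outcome.** The main mixed model has arm, period and arm-by-period terms and serves the 6-month SPPB change. A further longitudinal SPPB model is only to be considered; its visits, arms and contrast are not given.
- **Statistical analyses, Secondary outcomes.** The primary-outcome analysis is applied to "evaluate the change of the secondary outcomes between the inclusion and the 6-month follow-up visit". Then: "The analysis of the change of secondary outcomes in the interventional group will be performed using a longitudinal mixed effect linear model", with period as fixed effect, random centre, GP and patient, and adjustment for age. A last analysis looks for factors associated with SPPB at 6 months, again in the intervention group.

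**The concern.** The objective and the outcome section promise a 12-month horizon, and the objective makes it a comparison between randomised arms. The analysis section then sets a between-arm comparison that ends at 6 months and a longitudinal model that leaves out the control arm. An analyst who follows it literally produces no randomised evidence on whether any benefit lasts to 12 months.

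The only committed analysis that could use month-12 data is then a before–after change in the intervention arm. Patients enter with SPPB below 10, so improvement through regression to the mean is to be expected, and natural course is mixed in as well. The sample-size section itself assumes that controls gain 1.2 SPPB points. If the month-12 contrast is chosen only after the data are seen, it becomes post hoc.

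**Working it through.** The point rests on wording and schedule. The first step sets the promises against the analyses.

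**1. Promise against analysis**

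| Item | Month 6, between arms | Month 12, between arms |
|---|---|---|
| Objective (Background) | yes | yes |
| Outcome section, secondary outcomes | change to be analysed | change to be analysed (arms not specified) |
| Table 3, data in both arms | yes for most outcomes | yes |
| Main mixed model for SPPB change | yes | no |
| Same analysis applied to secondary outcomes | yes | no |
| Longitudinal model, secondary outcomes | no (intervention arm only, no arm term) | no (same reason) |
| Factor analysis for SPPB at 6 months | no (intervention arm only) | no |
| Optional longitudinal SPPB model | not stated | not stated |

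The last column contains no committed arm contrast for any outcome.

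**2. Table 3 by outcome**

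- SPPB, walk distance, physical activity, ADL/IADL, SF-12, serious falls, and weight/BMI: months 6 and 12 in both arms. A two-arm analysis over both visits is possible with scheduled data.
- Hospitalization: baseline and month 12 only.
- Institutionalization: month 12 only.

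The last two are listed secondary outcomes. An analysis of change from inclusion to month 6 has no month-6 value for either, so the stated comparison cannot be run for them.

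**3. The sample size**

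The plan's figure of 28 GPs per arm can be reproduced. Inputs from the sample-size section: difference 0.8, SD 1.7, ICC 0.15, 5 patients per GP, power 80%. Two-sided alpha 0.05 is assumed, as that section states none.

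- Design effect: 1 + (5 − 1) × 0.15 = 1.6.
- If 1.7 is the within-GP SD, total SD = 1.7 / √(1 − 0.15) = 1.844.
- GPs per arm = 2 × (1.844 × (1.960 + 0.842) / 0.8)² × 1.6 / 5 = 26.7. With iterated t quantiles on 2(k − 1) degrees of freedom it is 27.7, so 28.
- If 1.7 is the total SD, the same steps give 22.7 (normal) or 23.7 (iterated t), so 23 or 24.

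The section names no visit, but the primary outcome is the 6-month SPPB change, so the calculation belongs to month 6. It contains nothing for month 12.

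**4. Would a month-12 contrast be informative? (illustration)**

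Assume the same 0.8 points, SD and ICC at month 12, 30 GPs per arm, and a patient loss of 0% to 40%; the document gives no loss rate. Retained patients per GP are m = 5 × (1 − loss), the standard error is SD × √(2 × [1 + (m − 1) × 0.15] / (30 × m)), and power is Φ(0.8 / SE − 1.96).

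| Loss | m | Power, total SD 1.844 | Power, total SD 1.7 |
|---|---|---|---|
| 0% | 5 | 84% | 90% |
| 20% | 4 | 80% | 86% |
| 40% | 3 | 72% | 79% |

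On these assumptions the contrast is worth stating.

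**The case against.** The strongest reply is that this is a condensed article and that the model for a secondary time point is commonly left to the SAP. The outcome section does commit to analysing change to 12 months without restricting it to one arm. The statistical section does not say that its analyses are the only ones, and the optional longitudinal SPPB model could include both arms and month 12.

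Part of this stands. The optional model means that 12-month control data are not ruled out of every analysis. But it is optional, is described with SPPB as the independent variable, names no visit or contrast, and does not reach the secondary outcomes. Nor is the statistical section silent: it positively fixes the between-arm comparison at 6 months and the longitudinal model in one arm. An SAP faithful to that text would depart from the objective, and the reverse also holds.

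It is also fair that describing change within one arm is legitimate as a supplement, and that the protocol does not call it the programme's effect.

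Four stronger readings are tempting, and the document does not support them:

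- A reader might infer that 1.2 / 2.0 = 60% of the reported within-arm change is not due to the programme. Those are SPPB planning values for the primary outcome, which is compared between arms. The one-arm model concerns other outcomes, for which no planning values are given.
- A reader might infer that the month-12 visits of 30 × 5 = 150 control patients go unused. The text supports only that no committed analysis uses them.
- A reader might infer that the 12-month question cannot be answered. It can: the visits are scheduled in both arms, and only the contrast is missing.
- A reader might infer that muscular force is unmeasured. The SPPB is described as covering strength/endurance and includes timed chair rises, so this is a minor wording matter.

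**Conclusion.** The concern holds as an internal contradiction. The 12-month part of the main objective has no committed randomised comparison, and the stated 6-month analysis cannot be carried out for hospitalization or institutionalization. This rests on reading the statistical section as written and on the Table 3 entries.

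The bias of a one-arm before–after reading is real in kind, but its size for the secondary outcomes or at month 12 cannot be derived from the document. The 1.2-point gain expected in controls shows only that the protocol itself anticipates improvement without the programme.

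The 6-month primary outcome is defined consistently; its randomised comparison, the sample size and the data collection are unaffected. The point should be fixed, but it does not threaten the main result.

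**What to change.** Reconcile the objective, both sections on secondary outcomes, and Table 3, before outcome data are compared by arm:

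1. For outcomes with entries at months 6 and 12, extend the between-arm mixed model to both arms and both follow-up visits. The follow-up values are the response. Fixed effects are arm, visit, arm × visit, baseline value, age and centre; random effects are practice and patient. Report the arm contrast at month 12 with its 95% confidence interval.
2. Name SPPB at month 12 as a secondary outcome.
3. Compare hospitalization and institutionalization between arms at month 12 with a model suited to count or binary data that accounts for clustering by practice. The model in item 1 does not fit them: neither has a month-6 entry, and institutionalization has no baseline entry.
4. The intervention-only longitudinal model may stay if it is labelled descriptive and not read as an effect of the programme.
5. Optionally, tie the muscular-force wording of the objective to the SPPB strength/endurance component.

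The cost is analysis wording and programming. No visit, measurement or patient is added.

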### Participants

All subjects aged over 70 years old will be eligible except patients with functional or locomotor disabilities, a life expectancy less than 6 months, a progressive chronic disease affecting participation in the program, or a MMSE< 20.

For each consecutive patient over 70 years of age without exclusion criteria, GPs will screen patients with medical interview to detect 2 or more inclusion criteria described in Table 1. These criteria are partly derived from the sarc-f screening tool for sarcopenia [28].

**Table 1 Tab1:** Summary of eligibility, inclusion, non-inclusion and exclusion criteria

Eligibility criteria	Inclusion criteria	Exclusion criteria
Difficulty lifting packages over 4.5 Kg	Age > 70	Patient refusal to participate to the study
Difficulty rising from low seats without help of arms	SPPB <10	Functional or locomotor disabilities
Difficulty climbing less than 10 steps of stairs	≥ 2 eligibility criteria	Life expectancy less than 6 months
Difficulty moving or reduced walking speed		A chronic disease affecting participation to the program
Difficulty walking over 400 m without break		MMSE< 20
Walking time less than 1 hour per week		
Feeling of exhaustion during domestic activity		
> 2 falls during the last year		
Involuntary weight loss (> 5% in 1 month or > 10% in 6 months)		

In the presence of 2 or more inclusion criteria, GPs will assess the patient using the Short Physical Performance Battery (SPPB) [29]. In the event of a SPPB score < 10 (out of 12), patients will be given 9 questionnaires grouped in a unique folder: Activity Scale for the Elderly (PASE) [30], weekly sedentary time inspired by Gardiner [31], Activity of daily living scale (ADL), Instrumental activities of daily living scale (IADL) [32], SF-12 scale [33], Mini-Nutritional Assessment (MNA) [34], EPICES score *(Evaluation de la précarité et des inégalités de santé dans les centres de santé (in French))* [35, 36], Charlson index [37], Geriatric Depression Scale (GDS) [38] (Table 2) that measure their autonomy, nutrition and physical activity, and will be proposed another medical appointment for inclusion in the study. If a patient refuses to participate in the study, this will be noted in the CRF.

**Table 2 Tab2:** List of questionnaires

List of questionnaires	
Physical activity	Activity Scale for the Elderly (PASE) [30]
	Weekly sedentary time inspired by Gardiner [31]
Autonomy	Activity of Daily Living scale (ADL)

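### The intervention-arm change-from-inclusion model is unsuited to falls: the inclusion value is pre-enrolment recall, entry depends partly on falls, and there is no control arm or time-at-risk term

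*Protocol article*

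**What the plan says.** The Secondary outcomes section under Outcomes and measurements says "The change of the secondary outcomes between the inclusion, 6, and 12-month follow-up will be analyzed". Its list includes "the number of serious injuries, hospitalizations, and institutionalizations, falls with healthcare consumption". Table 3 has a row "Serious falls assessments", marked at baseline and at 6 and 12 months in both groups.

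The Secondary outcomes section under Statistical analyses plans two analyses that matter here:

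- Between arms: "The analysis used for the primary outcome will be used to evaluate the change of the secondary outcomes between the inclusion and the 6-month follow-up".
- Intervention arm only: "The analysis of the change of secondary outcomes in the interventional group will be performed using a longitudinal mixed effect linear model". Its terms are period as the one fixed effect of interest, random effects for centre, GP and patient, and an adjustment for age at inclusion.

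Neither is restricted to outcomes measured as a state on the day of the visit, and no time-at-risk term is named.

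Under Participants, Table 1 lists nine eligibility criteria, one of which is "> 2 falls during the last year". Entry requires "≥ 2 eligibility criteria" and an SPPB below 10.

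**The concern.** Weight, SPPB and SF-12 are states that can be measured at inclusion and again later. Falls are events that accumulate over time. At inclusion no follow-up has elapsed, so the inclusion value can only be recall of a period before enrolment. For falls, the period effect therefore sets a pre-enrolment recall count against counts during follow-up.

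Two things can move that contrast when the programme does nothing. First, some patients qualify because they fell often in the preceding year, and their counts will tend to drop afterwards. Second, the period effect compares raw counts, so any difference in the time covered goes straight into the estimate. Replacing the linear model by a count model with the same period contrast would cure neither problem.

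At stake is a secondary result on falls in a trial about preventing loss of mobility. A within-arm decline could be read as programme benefit, with no control arm in the model to show otherwise. The between-arm analysis is written only for 6 months, so as the text stands the 12-month change rests on the single-arm model.

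**Working it through.** The plan gives no figure for falls, so there is none to reproduce. Its sample size calculation concerns SPPB and has no bearing here.

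**Step 1. Windows alone.** Take a constant fall rate, no treatment effect and no selection. With L months of recall and W months of follow-up counted, the expected ratio of follow-up to baseline count is W/L.

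- L = W: ratio 1, no artefact.
- L = 12, W = 6: 6/12 = 0.5, an apparent halving.
- L = 6, W = 12 (12-month count cumulated from inclusion): 12/6 = 2, an apparent doubling.

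The article states neither L nor whether the 12-month count runs from inclusion or from month 6. If it runs from inclusion, the two follow-up counts cover 6 and 12 months, and no single recall window matches both.

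**Step 2. Selection.** This is a simulation with assumed inputs, since the article gives no fall rate:

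- Each patient has a constant annual fall rate from a gamma distribution with mean 0.5, 0.8 or 1.2 and shape 0.5 or 1.0. Counts are Poisson given the rate.
- The other eight criteria are binomial with a mean of 1, 2 or 3 met, independent of falls.
- A patient enters with at least two of the nine criteria, one being more than two falls in the past year (both from Table 1). The SPPB threshold is not modelled.
- All falls are counted, and the treatment effect is zero.

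Apparent change in the mean count, as ranges over the six rate and shape settings:

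| Mean other criteria met | Entrants for whom the falls criterion was decisive | Equal windows | 12-month recall vs 6-month count | 6-month recall vs cumulative 0–12-month count |
|---|---|---|---|---|
| 1 | 5% to 20% | −11% to −17% | −56% to −58% | +66% to +78% |
| 2 | 2% to 7% | −5% to −7% | −52% to −53% | +87% to +90% |
| 3 | 0% to 2% | −2% | −51% | +96% |

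**Step 3. Check by hand.** The two artefacts multiply. At the ends of the equal-window range the selection factors are 1 − 0.17 = 0.83 and 1 − 0.02 = 0.98.

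- 12-month recall against 6 months: 0.5 × 0.83 = 0.415 (−58%) and 0.5 × 0.98 = 0.49 (−51%).
- 6-month recall against cumulative 12 months: 2 × 0.83 = 1.66 (+66%) and 2 × 0.98 = 1.96 (+96%).

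These agree with the table. Selection always pushes towards a reduction and is modest. The window effect is larger where it exists, and its sign depends on choices the article does not state.

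**The case against.** The strongest reply is that recall windows belong in the case report form or the full protocol, so the article's silence on them is no defect. That stands. The only look-back the article gives, one year, belongs to an eligibility item and cannot be assumed for the outcome.

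A reader might therefore infer too much in three ways.

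- *That a fall reduction is built into the design.* It is not. Under equal windows the artefact is small, and under one arrangement the text leaves open it is an increase.
- *That a falsely significant reduction is likely.* With a 12-month recall, constant Poisson rates, 140 patients (28 × 5) and clustering ignored, the chance of a significant decline at 6 months runs from 33% at 0.1 falls a year to 99% at 0.8. These figures rest on the borrowed look-back. With a 6-month recall the window artefact vanishes and the chance returns to 5%.
- *That the randomised comparison is biased too.* It is not: both arms share the same selection and windows.

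It is also fair that the eligibility item counts any falls while the outcome counts serious falls or those with healthcare consumption, so the selection link is indirect. Patients can enter with no falls at all.

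Finally, the within-arm sentence is generic, does not name falls, and claims no efficacy. It may be shorthand: institutionalization has no baseline entry in Table 3, so change from inclusion cannot literally apply to every listed outcome. That limits how firmly harm can be predicted. It also shows that the change template was not adapted to event outcomes, and followed as written it takes in falls.

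**Conclusion.** The point holds for one secondary analysis, the intervention-arm change from inclusion applied to falls. What the text fixes is enough: falls are included, the model has no control arm and no time-at-risk term, the inclusion value must be recall, and entry depends partly on recent falls.

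The expected bias from regression to the mean is towards a reduction, about 2% to 17% with equal windows. That range assumes mean rates of 0.5 to 1.2 falls a year, one to three other criteria met on average, and all falls counted. The corresponding figure for serious falls cannot be identified from the article. Unequal windows would add about a halving at 6 months, or a rise of 66% to 96% at 12 months once selection is included, depending on definitions not shown.

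The estimate therefore cannot be interpreted as an effect of the programme. The change is worth making, but the primary outcome and the randomised 6-month comparison do not depend on it.

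**What to change.** In the Secondary outcomes section under Statistical analyses:

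1. Exclude falls from the intervention-arm change-from-inclusion analysis.
2. Analyse post-inclusion falls between arms as rates over 0–6 and 0–12 months, using the same window in both arms and time at risk for each patient. A Poisson or negative binomial model with log time at risk as offset and a random GP effect would serve, adjusted for centre and age as elsewhere in the plan.
3. Use pre-inclusion fall history as a baseline covariate, not as the first period.
4. Describe any within-arm trend only over equal post-inclusion windows (0–6 against 6–12 months), shown beside the control arm.

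No extra visit is needed, because falls are already scheduled at baseline, 6 and 12 months in both arms. The cost is slightly more than wording: the case report form must let 0–6 and 6–12 month falls be separated and time at risk be derived, and whether it does so now cannot be seen from the article. The before-after statement on falls is lost.

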### Sample size calculation

The inclusion of 28 GPs per arm will provide a power of 80% to detect a difference of 0.8 points in SPPB score change between arms (1.2 points increase in the control group, versus 2 points in the intervention group), with 5 patients for each GP, an intra-cluster correlation coefficient of 0.15, and with a standard deviation of inter-individual variability of 1.7. Accounting for loss to follow-up, it is planned to randomize 30 GPs in each group, giving a total of 60 GPs and 300 patients (5 patients for each GP). The power of the study was calculated using the method described by Donner and Klar [40] and with the package CRTsize in the R program, version 3.3.1 (R foundation, Vienna, Austria).

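### The intervention-arm model for change in secondary outcomes has no term for within-GP correlation of change, so its intervals are too narrow wherever such correlation exists (minor)

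*Protocol article*

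**What the plan says.** The section on secondary outcomes under Statistical analyses describes three analyses.

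- The between-arm comparison of change from inclusion to 6 months, which reuses the primary analysis.
- A within-arm analysis: "The analysis of the change of secondary outcomes in the interventional group will be performed using a longitudinal mixed effect linear model", specified "with a fixed period effect and as random effects: the center, the GP, and the patient nested within the GP" and adjusted for age at inclusion. No GP-by-period or other random slope is named.
- A factor analysis "to identify the factors associated with the SPPB result at 6 months in the interventional group", with "as random effects the center, the GP and the patient nested within the GP, and as fixed effect the corresponding factor". No period term is listed.

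The Sample size calculation section plans the trial "to detect a difference of 0.8 points in SPPB score change between arms", "with 5 patients for each GP, an intra-cluster correlation coefficient of 0.15". The ICC therefore belongs to the change in the primary outcome. It is the only ICC in the article.

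**The concern.** The quantity of interest in the within-arm analysis is the period effect, that is, the mean within-patient change. Random centre, GP and patient intercepts describe differences in level. They do not describe GPs whose patients change more or less than average, and it is this second kind of variation that makes changes correlate within a GP. The listed model thus appears to handle clustering but does not do so for the estimate it is meant to deliver.

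The protocol gives reasons to expect some correlation. GPs carry out the evaluations at inclusion, 6 and 12 months (Study design), help patients complete the questionnaires (Feasibility), and work in an open-label trial (Discussion of the study design). A shift in how one GP assesses would move that GP's patients together.

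At stake are intervals that are too narrow and p-values that are too small for the within-arm changes. The analysis would be repeated over several outcomes, and it is the only one described for them that is not limited to 6 months.

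**Working it through.** **Inputs.** ICC of SPPB change 0.15, 5 patients per GP, SD 1.7, difference 0.8, 28 GPs per arm for 80% power and 30 randomized per arm (Sample size calculation). Assumed: two-sided 5% for the sample size, since alpha is not stated there, and a 95% level for the within-arm intervals. The article attaches that level to the primary model's fixed effects and to the factor model ("This analysis will provide the effect estimation of each factor with its 95% confidence intervals"), but not expressly to the change model.

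**The plan's own figure.** GPs per arm = 2·SD²·(1.96+0.84)²/0.8² × DE/5, with DE = 1 + (5−1)×0.15 = 1.6.

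- If 1.7 is the total SD: 22.7, or 23.7 with t quantiles, so 23 to 24 GPs.
- If 1.7 is the SD within GP, the total SD is 1.7/√0.85 = 1.844: 26.7, or 27.7 with t quantiles, so 28 GPs, with 80.5% power.

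The second reading reproduces the stated 28. The planning does use a design effect of 1.6 on the change in SPPB.

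**Why the intercepts cancel.** Write the score of patient i of GP j at visit t as period(t) + centre + GP(j) + patient(ij) + error(ijt). The change between two visits is the difference of the two period terms plus the difference of the two errors; centre, GP and patient drop out. With balanced data the model's standard error is SD(change)/√N, as if the N changes were independent. In one simulated data set of 30 × 5 patients, a mixed-model fit gave 0.1530, equal to SD(change)/√150.

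If the changes have within-GP correlation ρ, with m patients per GP, the true standard error is larger by √DE, where DE = 1 + (m−1)ρ. Coverage of the nominal 95% interval is 2Φ(1.96/√DE) − 1.

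**Results at 5 patients per GP:**

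| Assumed ICC of change | DE | √DE | Coverage |
|---|---|---|---|
| 0.01 | 1.04 | 1.02 | 94.5% |
| 0.05 | 1.20 | 1.10 | 92.6% |
| 0.10 | 1.40 | 1.18 | 90.2% |
| 0.15 | 1.60 | 1.26 | 87.9% |

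With 3 patients per GP and ICC 0.15, DE = 1.3 and coverage is 91.4%.

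**Simulation at ICC 0.15, 5 per GP.** The paired-change form, which equals the intercept-only model with two balanced visits, covered 88.1% with 28 GPs and 87.7% with 30 (40,000 trials each). With three visits and 30 GPs it covered 87.6% (20,000 trials). Analysis at GP level restored 95.0% and 94.8% for 28 and 30 GPs. Direct mixed-model fits gave 90% in 200 runs; the simulation error there is √(0.9×0.1/200) = 2.1 points, so this agrees.

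**Factor model.** It has no period contrast, so its intercepts stay in the estimate. Simulated coverage for a GP-level factor was 95.5% (200 runs).

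**The case against.** *The ICC belongs to another outcome.* This stands. A reader might infer that the plan's 95% intervals cover 88%. The documents do not support that: 0.15 is stated for SPPB change and nothing is stated for PASE, walking distance, SF-12 or weight. The 88% is one row of a conditional table.

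*Not every secondary outcome is affected.* This stands. In Table 3 the MNA is taken at baseline only and institutionalization at 12 months only, so neither has a period contrast. Falls, hospitalizations and serious injuries are events or counts, to which coverage figures for a normally distributed change do not carry over.

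*The section's other longitudinal model is sound.* This stands. It would be wrong to say that the intervention-arm models share the defect, since the factor model has no period term.

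*The model may take change from inclusion as its response.* The random GP effect would then already sit on the change and the problem would vanish. The adjustment for age hints this way, because an age main effect does nothing for a period contrast on raw scores. But with change as the response, the fixed period effect would compare follow-up visits and would not estimate change from inclusion. The raw-score reading fits better, though the text does not settle it.

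*A condensed article leaves covariance structure to the analysis plan.* This stands only in part. The article never says intercepts only, but it lists the random terms, and following that list gives the problem described.

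*It is only a before-after analysis in one arm.* This stands and limits the weight. Such a change cannot support an efficacy claim at any coverage.

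**Conclusion.** The point holds in a narrow form and is minor. As listed, the within-arm model for change leaves any within-GP correlation of change out of its standard error, while the sample size section assumes such correlation for the SPPB. Any positive ICC errs in the same direction, towards intervals that are too narrow. The loss is negligible at an ICC of 0.01 (94.5% coverage) and material at 0.15 (87.9%).

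This rests on three assumptions: the random effects are intercepts on raw scores, there are about 5 patients per GP with balanced visits, and the outcome is continuous and measured repeatedly. It does not extend to the randomized comparison, to the factor model, or to the optional longitudinal SPPB model in the primary outcome section, whose random effects are not listed.

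**What to change.** In the within-arm model for change of secondary outcomes, add a random GP-by-period effect, and a centre-by-period effect where it can be estimated. Alternatively, analyse each patient's change from inclusion with a random GP effect. In either case, state whether the response is the score or the change, which removes the ambiguity. Leave the factor model as it is on this point.

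The cost is one model term and no new data. Intervals widen by √DE: about 2% at an ICC of change of 0.01, 10% at 0.05, 18% at 0.10 and 26% at 0.15.
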